### Overview of study design and objectives

In order to address service connection and availability of community-based substance use EBIs for YIJJ, we propose to partner with community mental health centers and juvenile justice systems in two Midwestern counties to: (1) implement universal substance use screening for probation youth (at the point of arrest) to determine substance use risk level and appropriate treatment needed; (2) implement and evaluate the feasibility and effectiveness of a brief substance use intervention for youth with mild/moderate substance use problems in community mental health centers; and (3) implement a comprehensive adolescent-specific evidence-based substance use treatment in community mental health centers. We propose to utilize a hybrid type 1 clinical-effectiveness-implementation trial [37] in order to evaluate facilitators and barriers to implementing this approach as well as test the effectiveness of these interventions in reducing substance use among YIJJ.

## Method

### Implementation model

Implementation will be guided by the Exploration, Preparation, Implementation, and Sustainment (EPIS) framework to study how best to implement the bundled treatment approach in juvenile justice settings and CMHCs [38]. We will utilize the Stages of Implementation Completion (SIC) implementation approach to measure inner and outer context factors that affect implementation of best-practices [38–41]. The outer context, in this case, includes state and local policies regarding funding and provision of addiction services for youth in general and, specifically, for justice involved youth. Inner context includes the organizations climate, culture, staffing as well as characteristics of juvenile justice and community mental health center (CMHC) staff towards adolescents (see Fig. 1 for illustration of EPIS model). The EPIS framework also explicitly identifies project phases, including exploratory phases, which is useful in the conceptualization of our pilot project. To guide and assess implementation we will collect data from self-report surveys and interviews conducted with substance use providers, parents, youth and court personnel across the study period.

**Fig. 1 Fig1:**
[figure not shown]
EPIS implementation model

### Study setting

Two counties in a Midwest state were chosen based on high rates of substance-related arrests and rates of substance use among adolescents in the community. Counties were chosen given their small size as well as the presence of one primary community mental health center (CMHC) that is designated to serve the community. This allows for feasibility of building and strengthening relationships between juvenile justice and community mental health professionals/agencies.

### Participants

#### YIJJ and caregivers

We will recruit YIJJ aged 14–17 in one of two counties who are either detained in the detention center and returning to the community or currently in the community. Eligible youth will be those who are identified as having a history of substance use, based on screening done by the juvenile justice staff (see below for explanation). Both youth and their legal guardian must agree to participate. Only youth and caregivers who are fluent in English will be eligible to participate.

#### Community partner participants

Community partner participants will be clinicians, case managers, and supervisors working in the CMHC in each county (range n = 10–30). Bachelor’s level case managers from each CMHC site (n = 2 case managers for each county) will be recruited to act as intervention specialists. They will be trained in the brief intervention and provide treatment to YIJJ and their caregivers. Master’s level licensed clinicians from each CMHC (n = 2 for each county) will be trained in the comprehensive substance use intervention and provide treatment to YIJJ.

The juvenile justice system in each county have agreed to participate and implement substance use screening. Designated juvenile probation officers/intake officers will be identified and will be responsible for conducting universal substance use screening with all youth coming through the detention center at intake.

In addition to these primary individuals who will provide interventions, we will seek participation from other personnel (e.g., juvenile justice intake staff, CMHC supervisors) who are involved in the implementation and sustainability of the interventions to complete qualitative interviews and quantitative measures to assess feasibility and implementation in these settings.

### Training and fidelity monitoring

#### Juvenile justice substance use screening

We will conduct a one-time training for juvenile probation officers at each of the JJ system sites to train them on the substance use screening tool (see below for details). Training is minimal compared to the intervention training given the ease/usability of the measure.

#### Interventions

Prior to the start of the trial, therapists and intervention specialists at each of the two sites will be trained by respective intervention training teams (i.e., training team for Teen Intervene and ENCOMPASS). Bachelor’s level brief intervention specialists will be trained in the brief interventions. For the purposes of wider dissemination of these evidence-based brief interventions, non-research providers at each CMHC also will have the opportunity to receive initial training. Following a one-time initial training, brief intervention specialists will have monthly meetings with the training team for ongoing training, consultation, and fidelity monitoring. Master’s level therapists who will be designated as ENCOMPASS therapists at each of the sites will be trained in ENCOMPASS by the ENCOMPASS master trainers. Following initial in-person training, ENCOMPASS therapists will engage in weekly meetings with the ENCOMPASS trainers for ongoing training, consultation, and fidelity monitoring. Psychotropic medication prescribers are also engaged in the weekly meetings and supervision is provided by an adolescent addiction psychiatrist.

##### Fidelity monitoring

Fidelity monitoring for the brief intervention and ENCOMPASS will be conducted by the respective intervention trainers.

*Teen Intervene* Brief intervention specialists will complete self-rating checklists following each session and also audiotape sessions to be rated by Teen Intervene trainers for fidelity [28]. Therapists and raters will complete the same checklists, which include items related to module-specific activities as well as items related to adherence to principles of motivational interviewing (e.g., reinforcing change talk) and cognitive behavioral techniques (e.g., assigning homework). Items are rated on a 5-point scale, with higher scores denoting greater fidelity/adherence and competency in skills. Mean scores of 3 across all items denote sufficient competency and fidelity.

*ENCOMPASS* ENCOMPASS therapists will complete self-rating treatment adherence fidelity checklists following each session as well as audio record sessions to be reviewed by ENCOMPASS trainers for fidelity checks. The same checklist will be used by therapists and raters to measure adherence and consists of six items related to principles of cognitive behavioral therapy six items related to principle motivational interviewing and motivational enhancement techniques, as well as items related to module-specific tasks and activities. Therapists self-rate their performance for each session in each of these areas on a 6-point scale (0 = not completed, 1 = low skill level to 5 = high skill level); thus, fidelity to the treatment can be quantified as an overall mean score for each session. Overall mean scores of 3 or above on the self-rating forms and/or trainer ratings of audiotaped sessions will be considered meeting minimum fidelity/adherence standards [32, 33].

### Procedures

#### Screening and referral

Juvenile probation officers will screen all youth who come through the intake process at the detention center using the CRAFFT [42]. The CRAFFT consists of six yes or no questions regarding substance use (e.g., do you ever use alcohol or drugs to relax; has family ever been concerned about your alcohol or drug use) as well as questions regarding frequency of past year substance use, with higher scores (range 0–6) denoting more severe substance use problems (see Additional file 1: Appendix S1 for complete measure). The CRAFFT has been shown to be an effective clinical tool in identifying substance use risk level among children and adolescents [41]. The research team will be notified of any youth scoring at least a 1 on the CRAFFT measure. Participants also will be notified of the opportunity to participate in an intervention and will be told that they might be contacted regarding voluntary participation in a research study. The research team will contact potentially eligible participants.

#### Enrollment and baseline assessment

Following initial recruitment, research assistants will complete consent/assent with the caregiver/youth at their home or preferred location. As part of the consent process, participants will be told that this is an intervention study and that they might be assigned to different interventions. Participants and their caregivers also will complete a baseline assessment, which includes self-report measures of demographics, family functioning, mental health, substance use (see Table 1 for overview of all measures).

**Table 1 Tab1:** Overview of data collection

	Informant	Content	Time of Completion
*Implementation measures*			
System-level implementation	CMHC staff, JJ staff, supervisors	Implementation Citizenship Behavior Scale [47], Implementation Climate Scale [48], Implementation Leadership Scale [49], Organizational Readiness to Implement Change (ORIC) [50] Qualitative interviews	Pre-, post-implementation
	JJ staff, supervisors	Qualitative interviews	Pre-, post-implementation
Intervention fidelity monitoring/adherence	Intervention providers	Brief intervention fidelity self-rating checklists ENCOMPASS treatment adherence checklist	Weekly
	Intervention trainers	Fidelity monitoring checklists based on therapist recorded sessions	Monthly
Treatment satisfaction	Parent, youth	Service Satisfaction Scale [51]	1-month post-intervention
Treatment response	Youth	BSCQ [42], FCU Clinical Monitoring Report [43], BSTAD [52]	Post 1st and 2nd intervention
*Participant*-*level measures*			
Demographics	Youth, parent	Family affluence [53], Family characteristics	Baseline
Substance use	Youth	CRAFFT [50], BSCQ [51], BSTAD, AUDIT-C [54]	Baseline, 3-, 6-months
Family functioning	Youth, parent	Parental Monitoring Scale [55]	Baseline, 3-, 6- months
Health service use history	Parent		Baseline, 3-, 6-months
Psychosocial functioning	Youth, parent	Difficulties in Emotion Regulation Scale [56], Peer Conflict Scale [57], Hope & Life Satisfaction Scales [58]	Baseline, 3-, 6-months
Mental health	Youth	K-CAT (computerized child diagnostic evaluation; [59])	Baseline, 6-months

All measures are self-report unless noted otherwise

#### Risk level determination

Based on the youth’s initial CRAFFT score as well as their scores on initial baseline measures collected after consent at the first/baseline visit, youth will be categorized as either low to mid-risk or high-risk based on criteria from the American Society of Addiction Medicine (ASAM). ASAM criteria utilizes six dimensions of an individual’s substance use and overall functioning to determine appropriate level of care [25]. We will determine risk level based on youth’s pattern of substance use, such as frequency and quantity of use, as well as problematic use based on DSM-5 substance use disorder symptoms. Table 2 describes specific risk determination criteria we will determine based on assessment. Generally, high-risk youth will be those who have identified past year repeated use of more lethal substances with a high risk for overdose and withdrawal potential (e.g., opioids, methamphetamine) and those who endorse three or more DSM-5 SUD symptoms, which is consistent with a moderate to severe SUD. All other youth initially will be randomized to one of the brief interventions. Based on preliminary data collected from each county, it is estimated that about 10% of youth will be in the high-risk group.

**Table 2 Tab2:** Risk level determination

	Brief intervention (low/mid risk)	Comprehensive intervention (high risk)
Substance use frequency	Less than weekly use of cannabis, alcohol, nicotine	Weekly or more frequent use of any substance Past year repeated use of lethal substance (opioids, methamphetamine, benzodiazepines)
Problematic substance use	Minimal problems or consequences of use ≤ 2 DSM-5 SUD symptoms	History of overdose Report of experiencing withdrawal ≥ 3 DSM-5 SUD symptoms

Following determination of risk level, high-risk youth will be assigned to complete ENCOMPASS, the comprehensive substance use treatment. Youth who are categorized as low- or mid-risk will be randomly assigned to one of the two brief interventions. Following randomization, youth will engage in either Teen Intervene or Family Check-Up with a brief intervention specialist.

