##### Measuring treatment response

Following completion of the first round of brief interventions (three sessions of Teen Intervene), we will measure youth’s response to treatment. Treatment response will be measured utilizing the Brief Situational Confidence Questionnaire (BSCQ), an eight item self-report measure of one’s level of confidence in resisting urges to use substances in eight situations: unpleasant emotions, physical discomfort, pleasant emotions, testing of control, urges and temptations, conflict with others, social pressures, and pleasant times with others [42]. Individuals rate their confidence in abstaining from substance use in each of the situations on a 0% (*not at all confident*) to 100% (*completely confident*), with higher scores denoting greater confidence in abstaining from substance use. Treatment response will be determined utilizing a cut-off overall mean score of 70% on the BSCQ (i.e., average of 70% confidence in abstaining from using substance use across all eight scenarios), based on results from previous studies utilizing the BSCQ as a measure of symptom improvement [43]. The cutoff of 70% has two advantages: it is the average treatment response expected for this intervention, and it yields (approximately, if the distribution is symmetric) an anticipated equal sample-size split for responders and non-responders for the second randomization. Those with a post-intervention score of 70% or higher will be considered “treatment responders” and those whose BSCQ post-intervention score is lower than 70% will be considered “treatment non-responders.” Those youth who are considered “responders” will be told that they have successfully completed the intervention; they will complete additional post-treatment measures at 3 and 6 month follow-up. Non-responders will continue to the second randomization.

Following completion of treatment response measures using the BSCQ, those who are identified as “non-responders” (i.e., mean post-test BSCQ score lower than 70) will complete a second round of brief interventions. If youth continue to not respond, clinicians will make recommendations and referrals as appropriate. Following completion of the second round of brief intervention, treatment response will be measured again using the BSCQ and participants will complete 3- and 6- month follow-up (see Fig. 2).

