**Fig. 2 Fig2:**
[figure not shown]
Overview of study design. YIJJ who score 1 or more on the CRAFFT will be recruited for the study. If interested and consent to treatment, they will be assessed to determine risk level. YIJJ identified as high-risk youth will be assigned to complete ENCOMPASS. Low to mid risk youth will be assigned to the brief intervention, Teen Intervene. Following the brief intervention, we will measure treatment response using the BSCQ. YIJJ who score below 70% will be considered “non-responders” and referred to ENCOMPASS

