### Data analysis

#### Measurement of intervention effectiveness and treatment response

##### Preliminary analyses

Preliminary analyses will be used to compare the primary treatment response outcome (confidence of abstaining measured by the BSCQ) and substance use outcome across the responders and non-responders of the brief intervention and ENCOMPASS at baseline, 3 months, and 6 months. A separate model will be utilized to measure effectiveness among those assigned to ENCOMPASS. Substance use will be calculated as number of days in the past month of using alcohol, marijuana, and other substances (range 0–90). These outcomes will be compared between groups with longitudinal generalized linear models (GLM) using the GENMOD procedure with a linear link and normal error distribution. The BSCQ and substance use outcome will be analyzed in separate models. The baseline measure of BSCQ or substance use days will be adjusted as covariates and the repeated measurements of each outcome at 3 months and 6 months will be analyzed simultaneously in the model.

The GLMs are easily fit for non-Gaussian distributions by specifying appropriate link functions and error distributions. If substance use days exhibit sparse counts or large frequency of zeros, we will consider using logistic, Poisson, or zero-inflated Poisson regression models, depending on the observed distributions of outcome behaviors. We also will explore analyzing substance use as time-to-event data using a Cox proportional hazards regression model with the SAS PHREG procedure with censoring if loss to follow-up occurs. Effect sizes will be computed from the model as differences between groups on adjusted means divided by SDs for the linear models, or differences between odds for logistic models or hazards for Poisson models.

The median and relevant percentile (e.g. 25th or 75th) of time to events will be presented by group with associated confidence intervals. All models will include an indicator variable for whether the subject was enrolled as a detained or probation youth. Other covariates will be included based on their theoretical importance as potential confounders and on their imbalance between randomized arms at baseline. We also will examine moderators that we have hypothesized to be potential determinants of treatment response (e.g., family functioning).

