##### Sample size and power

We plan to recruit n = 80 youth and caregiver dyads per county (160 total). We estimate that no more than 10% of youth in each county will be high-risk, resulting in a sample size of n = 16 assigned to ENCOMPASS and n = 144 to first-stage brief intervention (BI). We anticipate 20% loss at 6-month follow-up resulting in n = 12 in the ENCOMPASS group and n = 116 in the first-stage BI with 6 month data (58 responders and 58 non-responders, assuming a 50% response rate. We have accounted for a sample size inflation factor related to potential within-county intraclass correlation (ICC) of outcomes. Specifically, in the first step of the back-calculation, we determined that a sample size of n = 40 per responders and non-responders to the first-stage intervention (with 6-month data) is required under the “independence of observations” assumption (i.e., *before* accounting for clustering) to provide 80% power for the two-sided model-based tests to detect an effect size (0.63) that is between medium (0.50) and large (≥ 0.80). For a first-stage effective sample size of 40 in each group (responder vs. non-responder), there is a 1.39 sample size inflation factor (IF) when the ICC = 0.01 and the number of clusters (i.e., counties) = 2: IF = [1 + (average 40 patients per cluster − 1) × ICC of 0.01]. Therefore, an actual sample size of 56 per first-stage brief intervention (i.e., 40 × 1.39) with 6-month data is required (i.e., an effective sample size of 40 per first-stage brief intervention with 6-month data if observations were not clustered). The sample of 56 in each group will provide adequate power for this feasibility study and its preliminary hypothesis tests, given that we anticipate n = 58 per first-stage group (responder vs. non-responder) with 6-month data. This power calculation is conservative because the longitudinal models will have slightly increased power due to incorporating all available data (baseline, 3-months, 6-months), including data from persons missing one but not all times points. The goal will be to estimate effect sizes, for which the planned sample size will be adequate. A minimum of 12 per group is recommended for estimating effects sizes of continuous outcomes in pilot or feasibility studies [44].

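### The article gives two incompatible allocation schemes for low/mid-risk youth (randomised to Teen Intervene or Family Check-Up; all to Teen Intervene), and the non-responder pathway and analysis text do not fit either one throughout

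*Protocol article*

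**What the plan says.** Some sections describe a randomised comparison of two brief interventions:

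- Risk level determination refers to randomisation of low/mid-risk youth three times, including "Youth who are categorized as low- or mid-risk will be randomly assigned to one of the two brief interventions" and "Following randomization, youth will engage in either Teen Intervene or Family Check-Up with a brief intervention specialist".
- Measuring treatment response refers twice to a second randomisation.
- Table 1 lists an FCU (Family Check-Up) clinical monitoring report among the treatment-response measures.
- Preliminary analyses selects covariates partly "on their imbalance between randomized arms at baseline".

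Other sections describe one brief intervention with no randomisation:

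- Fig. 2 caption: "Low to mid risk youth will be assigned to the brief intervention, Teen Intervene".
- Measuring treatment response: "Following completion of the first round of brief interventions (three sessions of Teen Intervene), we will measure youth’s response to treatment".
- Overview of study design and objectives sets out a single brief intervention.
- Training and fidelity monitoring names training teams and rating checklists for Teen Intervene and ENCOMPASS only.

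For youth below the 70% BSCQ cut-off, Measuring treatment response gives a second randomisation and a second round of brief interventions. The Fig. 2 caption refers them to ENCOMPASS.

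Preliminary analyses compares responders, non-responders and ENCOMPASS. Sample size and power sets its requirement for responders against non-responders, then calls the inflated figure "an actual sample size of 56 per first-stage brief intervention".

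**The concern.** Whether minors are randomised, and to what, is the basic fact of the design. Two sites working from this article could allocate youth differently, and no later analysis could repair that.

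The analysis text is coherent under neither scheme. With randomisation, the contrast it creates at the first stage (Teen Intervene against Family Check-Up) does not appear among the planned comparisons. Without it, the covariate rule has nothing to act on, and the only powered contrast separates youth by how they scored after treatment. Either way, the stated aim of testing effectiveness is not served by the comparison that is powered.

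**Working it through.** **Allocation.** Risk level determination sends low/mid-risk youth by chance to one of two interventions. The Fig. 2 caption sends all of them to one. The definition of the first round, as three Teen Intervene sessions, leaves no room for a Family Check-Up arm. Family Check-Up has no training or fidelity plan in the article, yet its monitoring report is still in Table 1. All of this is current text.

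**Non-responders.** A second randomisation and a second brief round could be parts of one scheme. Referral to ENCOMPASS, as in the caption, is a different one.

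**Sample size.** Inputs from Sample size and power: effect size 0.63, 80% power, two-sided, ICC 0.01, 2 counties, 160 recruited, 10% high-risk, 20% loss, 50% response. Alpha is not stated; 0.05 is assumed.

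1. Per group before clustering: 2(1.960 + 0.842)² / 0.63² = 15.70 / 0.397 = 39.6, so 40, as stated.
2. Inflation: 1 + (40 − 1) × 0.01 = 1.39; 40 × 1.39 = 55.6, so 56, as stated.
3. Anticipated with 6-month data: 160 − 16 = 144; 144 × 0.8 = 115.2 (the article gives 116).
4. Split by response at 50%: 116 × 0.5 = 58 per group.
5. Split by 1:1 randomisation (ratio assumed): 116 / 2 = 58 per arm.
6. Power at 0.63 with 58 per group: effective size 58 / 1.39 = 41.7, giving 82% under step 4 or step 5.

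Steps 4 and 5 coincide, so the numbers do not show which contrast they were meant for.

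**Second randomisation, if it exists.** 58 non-responders in two equal arms (assumed) give 29 per arm.

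| | Effective n per arm | Power at 0.63 | Effect detectable with 80% power |
|---|---|---|---|
| No clustering | 29 | 67% | 0.74 |
| Inflation 1.39 | 29 / 1.39 = 20.9 | 53% | 0.87 |

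The article gives no power for this stage.

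**Meaning of the powered contrast.** Responders and non-responders are defined by the post-intervention BSCQ mean. The BSCQ is also an analysed outcome at 3 and 6 months. Groups chosen on a variable will tend to differ on it later, whether or not the intervention worked. Baseline adjustment does not remove this, because the split is made after treatment.

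**The case against.** The strongest reply is that the analysis does name its comparison. Preliminary analyses sets out responders, non-responders and ENCOMPASS, and Sample size and power ties 40 and 0.63 to responders against non-responders and derives 58 from a 50% response rate. The conflicting label occurs in one sentence. This stands: a reader might infer that the power figure is undefined, but it is computable and mostly attached to one contrast, with one sentence mislabelled.

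Three other inferences also go too far.

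- A reader might conclude that a two-arm calculation was relabelled. The arithmetic cannot show this, since 58 arises under either split.
- A reader might conclude that families are misinformed at consent. Enrollment and baseline assessment says only that they may be assigned to different interventions, which stays true if risk level decides between Teen Intervene and ENCOMPASS.
- A reader might call Teen Intervene against Family Check-Up the only unbiased comparison. A second randomisation, if real, would create another.

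The Analyses section calls the tests preliminary because this is a feasibility study, and the stated goal is to estimate effect sizes. That lowers the demand on power, not the need for a single allocation scheme. The single-intervention sections are also not uniform: the Abstract and the training text use plurals for the brief intervention. That adds to the inconsistency.

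The article already adjusts for the baseline value and for detained or probation status, so no criticism is made there. A fuller protocol may hold more detail, but it cannot excuse two incompatible statements in the article.

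**Conclusion.** The contradiction is established by the text itself and must be fixed before enrolment. It covers first-stage allocation, the step after non-response, the covariate rule and one label in the sample-size paragraph. The stated 40, 1.39 and 56 are arithmetically sound, assuming alpha 0.05, and 58 anticipated per group gives about 82% power for whichever two-group split is meant.

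The damage lies in what is compared. Under randomisation, no comparison by assigned brief intervention is named, and a second randomisation would have about 53% to 67% power at 0.63 (two equal arms assumed). Under a single brief intervention, the powered contrast cannot show effectiveness. The documents do not settle which scheme is intended, and this point does not choose one.

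**What to change.** The sponsor should state one allocation scheme and one pathway for non-responders, then reconcile Table 1, Risk level determination, Measuring treatment response, the Fig. 2 caption, Preliminary analyses, and Sample size and power to them.

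- **If there is a single brief intervention:** remove all three randomisation references in Risk level determination and both in Measuring treatment response, together with Family Check-Up, the FCU report, the mention of randomised arms and the per-intervention label on the 56. Base effectiveness on within-group change from baseline, in line with the Abstract's reference to change across treatment, and acknowledge that there is no comparator. Present responders against non-responders as descriptive. The 40/56/58 calculation does not cover within-group change, so the sample-size justification needs restating.
- **If Family Check-Up is randomised:** add it to the objectives, training and fidelity sections. Add the comparison by randomised arm, with 56 per arm required and about 58 anticipated if allocation is 1:1. State that the power given does not cover any second randomisation.

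Under either option, check the consent wording against the scheme chosen; it may need no change. The cost is editing before enrolment: Data Availability states that data collection has not begun.
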